### Study design and setting

MagPEP is a randomized, placebo-controlled phase III trial, in which adult patients with a clinical indication for diagnostic or therapeutic ERCP are randomized to receive either magnesium sulphate or placebo 60 min before and 6 hours after the intervention.

The pathway by which patients are recruited and treated is shown in Figure 
1.

**Figure 1 F1:**
[figure not shown]
Randomization and treatment flow chart of the study.

### Patients

In all of the participating academic gastroenterology departments in Germany and Hungary, all adult (≥ 18 years of age) patients with a clinical indication for ERCP will be screened for eligibility for the trial. Exclusion criteria are listed in Table 
1. Only patients who have not previously undergone an ERCP will be included in the study.

**Table 1 T1:** Exclusion ciriteria

•	Previous ERCP
•	Known allergy or intolerance to one of the compounds used in the study
•	Participation in another interventional trial during the previous four weeks
•	Pregnancy and breast feeding
•	current acute pancreatitis
•	Renal insufficiency ≥ stage 4 (K/DOQI), i.e. MDRD-GFR < 30 ml/min/1,73 m^2^)
•	Hyperthyroidism
•	Symptomatic bradycardia <35 bpm
•	Atrioventricular block > 1° or other cardial conduction defects
•	Myasthenia gravis
•	Liver cirrhosis Child C
•	Overt coagulopathy
•	Kidney stone diathesis (calcium-magnesium-ammonium-phosphate stones)
•	Mental impairment, addiction or other disorders leading to the patients inability to understand the scope and possible consequences of a participation in a clinical trial
•	Magnesium medication within 14 days before the procedure
•	Inability to give informed consent

### Sample size considerations

Randomization of 502 patients (251 in each arm) will detect a 50% reduction in the relative risk of post ERCP pancreatitis in the treatment arm as compared to the placebo arm with 80% power (α-1 = 0.2) and a p-value of <0.05 (β-1 = 0.05). This figure assumes that the incidence of the primary end-point without preventive measures is 7.4%, which was the incidence of post-ERCP pancreatitis at the Department of Medicine A of Greifswald University Medicine in the period 2004–2005, and that the drop-out rate will be 5%.

#### Randomisation

Upon recruitment into the trial each patient will receive a unique identification number, making all patients identifiable for their local treating physician throughout the study. Only the local investigator will keep a personal list of patient numbers and patient names in order to recover records of the patients under his or her care after the end of the trial or for auditing purposes. After the patient's eligibility for randomisation has been assessed and written informed consent has been obtained, he/she will be randomly assigned to one of the two treatment arms (1:1 randomization) and receive a unique randomisation number, by which the order in which the patients are entered at the respective centre can be identified. Randomisation will be stratified by centre and reported to the PI-centre by fax within 24 h. The randomisation list will be kept under lock and key at the Department of Medicine A in Greifswald but will be accessible 24 hours a day in case of an emergency code break. Block randomization with blocks of four patients will be carried out centrally in the University Pharmacy Greifswald. The study is carried out in a double-blinded fashion.

### Treatment scheme

All randomized patients receive an intravenous infusion 60 min before the start and 6 hours after the end of ERCP. To prevent adverse reactions to magnesium, which are seen more frequently if the substance is injected rapidly, the first infusion is given over 60 min, the second infusion is given over 2 hours. In the magnesium arm 500 ml NaCl 0,9% containing 10 ml magnesium sulphate 50% (= 4930 mg magnesiumsulphate-heptahydrate; magnesium content: 486,1 mg = 20 mmol = 40 mval) will be administered. In the placebo arm 500 ml NaCl 0,9% + 10 ml NaCl 0,9% will be given in the same manner. Test substance vials are labelled with protocol and randomization number only giving no indication as to their content.

The ERCP intervention will be carried out according to the established clinical practice at the respective centre and in no way differently as compared to patients not participating in the study. After completion of the ERCP, the endoscopist is going to fill out a questionnaire on the details of the procedure, giving information e.g. on the final endoscopic diagnosis, the number of pancreatic duct injections, cannulation difficulties, the duration of the procedure, among other procedural details.

Six and 24 hours after ERCP patients are asked to assess their pain level using a visual analogue scale and the pain medication required and used is recorded. In addition, a clinical examination of the abdomen is performed and a blood sample is taken. To ensure blinding the clinician in charge of the patient is not allowed to order any tests on blood magnesium concentration unless in an emergency, which will lead to the exclusion of the patient. If post-ERCP pancreatitis develops blood samples, clinical examination, pain assessment and documentation of pain medication is continued until the day of discharge from the hospital.

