### Definitions

Acute post-ERCP pancreatitis is defined as the presence of typical abdominal pain at 24 hours post ERCP in combination with an elevation in serum lipase level to at least three times the normal upper limit. Severity of pancreatitis is classified according to the 1991 Consensus Guidelines published by Cotton et al.
[23]: mild pancreatitis leading to a prolongation of hospitalization by up to three days, moderate pancreatitis requiring four to ten days of hospitalization and severe pancreatitis involving hospitalization for more than ten days and evidence of necrotizing pancreatitis and/or infected necrosis or pseudocyst (fluid collection) development.

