### Follow-up

30 days after the ERCP all participants will be contacted by telephone in order to determine the 30-days morbidity and mortality as well as quality of life.

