### Safety considerations

The assessment of safety will be based mainly on the frequency of adverse events (AEs) and on the number of laboratory values falling outside of pre-determined ranges. AEs will be summarized by presenting the number and percentage of patients having any AEs or serious adverse events (SAEs) and for each individual AE. Furthermore, the most common AEs (those occurring in at least 10% of the respective group) will be determined. Any other information collected (e.g. severity or relatedness to study drug) will be listed as appropriate. Laboratory data will be summarized by presenting shift tables using normal ranges (baseline to most extreme post-baseline value) and by presenting summary statistics of raw data and changes from baseline values (means, medians, standard deviations, ranges). The analysis of safety and tolerability will be based on all patients entered into treatment who received at least one application of the study medication. All proportions will be given along with exact Pearson-Clopper 95% confidence bounds.

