### Statistical analysis

The primary analysis will be a comparison of magnesium versus placebo for the prevention of the primary end-point on an ‘intention to treat’ and ‘per protocol’analysis. Intention to treat and per protocol analyses will also be performed for the secondary outcomes. An interim analysis for monitoring safety issues and potential power calculation adjustments can be conducted by the data safety monitoring committee after half the patients have been recruited.

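### Exclusion after an emergency magnesium test has no stated scope and, read literally, conflicts with the intention-to-treat analysis, the safety set and the 30-day follow-up

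*Protocol article*

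**What the plan says.** All references are to the Methods of the protocol article.

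- **Treatment scheme.** To protect blinding, the treating clinician may not request a blood magnesium measurement "unless in an emergency, which will lead to the exclusion of the patient". The rule stands in the paragraph on the 6-hour and 24-hour assessments. It names no analysis set and does not say whether follow-up continues.
- **Statistical analysis.** Magnesium and placebo are compared on the primary endpoint "on an ‘intention to treat’ and ‘per protocol’analysis", and the same holds for the secondary outcomes. Neither set is defined.
- **Safety considerations.** The safety analysis is "based on all patients entered into treatment who received at least one application of the study medication". No exception is made for patients who had a magnesium test.
- **Follow-up.** At 30 days, "all participants will be contacted by telephone in order to determine the 30-days morbidity and mortality". Again there is no exception.
- **Randomisation.** An emergency code break is provided for, and no exclusion is attached to it.

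**The concern.** The rule acts after randomisation. The first infusion starts 60 minutes before ERCP, so any test ordered around the later assessments also comes after study drug. An exclusion at that stage is harmless only if it is unrelated to treatment and outcome, and here it may be related to treatment. The Treatment scheme section itself expects reactions to the drug: "To prevent adverse reactions to magnesium, which are seen more frequently if the substance is injected rapidly". Suspicion of such a reaction is an obvious reason to measure magnesium in an emergency, and true reactions can occur only in the active arm.

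Two comparisons are at stake. On safety, the patients removed could be those with the adverse events that matter most. On efficacy, the endpoint needs "the presence of typical abdominal pain at 24 hours post ERCP" together with raised lipase, so a patient excluded before that time may never be assessed. Sites would act on the wording as it stands, and a later analysis plan cannot recover data that were not collected.

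**Working it through.** **Step 1. The passages side by side.** Take a randomised patient who has had the first infusion and then has an emergency magnesium test.

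| Section | Status of this patient |
|---|---|
| Treatment scheme | Excluded, scope not stated |
| Statistical analysis | Belongs in the intention-to-treat comparison |
| Safety considerations | In the safety set (at least one dose received) |
| Follow-up | Contacted at 30 days |

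On the literal reading the first row cannot hold together with the other three. The conflict with the safety set is the firmest, because that set is defined in the text.

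**Step 2. Expected events.** The plan gives no number of emergency tests, so there is no figure of its own to reproduce on this point. The inputs are 251 patients per arm (Sample size considerations) and event rates of 7.4% and 3.7% (Study objectives). The figure of 251 is used only as the planned arm size; how it was derived is a separate matter.

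- Placebo: 251 × 0.074 = 18.6, taken as 19.
- Magnesium: 251 × 0.037 = 9.3, taken as 9.

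**Step 3. Sensitivity to single exclusions.** The test is the two-sided pooled two-proportion test (uncorrected chi-square), which is an assumption because the article names no test:

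z = (p₁ − p₂) / √[p(1 − p)(1/n₁ + 1/n₂)], where p is the pooled proportion.

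With no exclusions, p₁ = 19/251 = 0.0757, p₂ = 9/251 = 0.0359 and p = 28/502 = 0.0558. The standard error is 0.0205, so z = 0.0398/0.0205 = 1.94.

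| Patients excluded | Placebo | Magnesium | z | p |
|---|---|---|---|---|
| None | 19/251 | 9/251 | 1.94 | 0.052 |
| One magnesium case | 19/251 | 8/250 | 2.17 | 0.030 |
| Two magnesium cases | 19/251 | 7/249 | 2.40 | 0.017 |
| One magnesium non-case | 19/251 | 9/250 | 1.93 | 0.053 |
| One placebo case | 18/250 | 9/251 | 1.79 | 0.073 |
| Two placebo cases | 17/249 | 9/251 | 1.63 | 0.10 |

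Fisher's exact test starts at 0.078 and falls to 0.046 after one magnesium-arm case is lost.

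**Step 4. Bias when magnesium has no effect.** Assume a 7.4% risk in both arms and that a fraction r of the magnesium arm only is excluded, of whom a fraction q are cases. The remaining magnesium-arm risk is (0.074 − r·q)/(1 − r). Both r and q are assumptions.

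| r | q | Magnesium-arm risk | Apparent RR | Two-sided rejection rate |
|---|---|---|---|---|
| 2% | 7.4% | 7.4% | 1.00 | 5.0% |
| 2% | 25% | 7.0% | 0.95 | 5.3% |
| 2% | 50% | 6.5% | 0.88 | 6.7% |
| 2% | 100% | 5.5% | 0.75 | 13.7% |
| 5% | 25% | 6.5% | 0.88 | 6.9% |
| 5% | 50% | 5.2% | 0.70 | 17.5% |

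For example, with r = 2% and q = 50% the risk is (0.074 − 0.010)/0.98 = 0.0653, and 0.0653/0.074 = 0.88. If the excluded patients carry average risk, the primary endpoint is not biased.

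**The case against.** The strongest reply is that exclusion may mean something narrower. The sentence is about blinding and stands in a section on treatment, so it could mean leaving blinded treatment or the per-protocol set only. A per-protocol analysis is planned, and the safety and follow-up sections make no exception. Read that way, the sections agree. This is possible, but no section says so, and the wording names the patient without limit. That full set definitions may stand in a document not shown explains why they are absent here. It does not explain an exclusion rule stated without limit.

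A reader might also infer that the rule biases both efficacy and safety in favour of magnesium. For efficacy the documents do not support that. Nothing says that pancreatitis prompts a magnesium test, and the Treatment scheme section continues observation of pancreatitis cases until discharge. Losing placebo cases moves the result against magnesium, as Step 3 shows. The direction follows from whose cases are assumed lost.

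Two further points stand. The 19 versus 9 starting point lies close to 0.05, so the shift in p shows the fragility of a comparison with few events and does not measure this bias. Emergency tests may also be few: Table 1 excludes severe renal insufficiency, conduction defects and myasthenia gravis, and the Discussion describes adverse effects as infrequent and mostly mild.

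**Conclusion.** The point holds as a conflict on the literal reading, which the sections must resolve. An exclusion of unstated scope after randomisation cannot stand beside an intention-to-treat analysis, a safety set of all treated patients and follow-up of all participants.

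The link to treatment rests on the protocol's own expectation of magnesium reactions, so the safety comparison is the more exposed. A link to pancreatitis is inference only. The primary endpoint can be biased, but neither direction nor amount can be known without the number of tests. With about 28 expected events (19 + 9), one lost case moves p from 0.052 to 0.030 or to 0.073, depending on the arm. These are illustrations under the protocol's assumed rates and an assumed chi-square test. The documents do not establish that the trial would favour magnesium, or that tested patients would in fact be left out of the analysis.

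**What to change.** Reconcile the sections with a short statement in Treatment scheme, matched in Statistical analysis and in the site instructions:

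- An emergency magnesium measurement or code break is recorded as a protocol deviation.
- The 24-hour and 30-day assessments are still collected.
- The patient stays in the intention-to-treat set as randomised and, if at least one dose was given, in the safety set.
- Omission is allowed only from the per-protocol set.

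The change concerns follow-up and analysis only. It does not alter emergency care, the restriction on magnesium tests or any decision on further study treatment. It costs about a sentence of text and a note to sites, adds no assessments beyond those already planned, and leaves the planned 502 patients unchanged.

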### Follow-up

30 days after the ERCP all participants will be contacted by telephone in order to determine the 30-days morbidity and mortality as well as quality of life.

### Safety considerations

The assessment of safety will be based mainly on the frequency of adverse events (AEs) and on the number of laboratory values falling outside of pre-determined ranges. AEs will be summarized by presenting the number and percentage of patients having any AEs or serious adverse events (SAEs) and for each individual AE. Furthermore, the most common AEs (those occurring in at least 10% of the respective group) will be determined. Any other information collected (e.g. severity or relatedness to study drug) will be listed as appropriate. Laboratory data will be summarized by presenting shift tables using normal ranges (baseline to most extreme post-baseline value) and by presenting summary statistics of raw data and changes from baseline values (means, medians, standard deviations, ranges). The analysis of safety and tolerability will be based on all patients entered into treatment who received at least one application of the study medication. All proportions will be given along with exact Pearson-Clopper 95% confidence bounds.

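### Laboratory safety measures have no common time window, but only pancreatitis cases are sampled after 24 hours, so both measures are biased toward the arm with fewer cases

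*Protocol article*

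**What the plan says.** Two sections of the protocol article have to be read together.

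- **Sampling (Treatment scheme).** The common schedule is fixed by "Six and 24 hours after ERCP patients are asked to assess their pain level using a visual analogue scale"; at those visits "a clinical examination of the abdomen is performed and a blood sample is taken". The exception is outcome-driven: "If post-ERCP pancreatitis develops blood samples, clinical examination, pain assessment and documentation of pain medication is continued until the day of discharge".
- **Measures (Safety considerations).** Safety rests mainly on adverse events and "on the number of laboratory values falling outside of pre-determined ranges". Laboratory data are then shown as "shift tables using normal ranges (baseline to most extreme post-baseline value") and as "summary statistics of raw data and changes from baseline values (means, medians, standard deviations, ranges").
- **Population (Safety considerations).** The safety set is "all patients entered into treatment who received at least one application of the study medication", so pancreatitis cases are included.

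The laboratory summaries have no time window and are not restricted to the scheduled samples. How often cases are sampled before discharge, and for which analytes, is not stated.

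**The concern.** How long a patient's laboratory values are observed depends on whether that patient reaches the primary end-point, and treatment is meant to change that end-point. A count of abnormal values and a worst value per patient both increase with the number of samples. The extra samples also come from patients who are ill. If magnesium prevents pancreatitis, placebo gains abnormal values simply because more placebo patients are still being sampled. If it prevents none, the distortion disappears in expectation. The laboratory comparison would then partly restate the efficacy result and could mask a small or moderate laboratory harm. The same tables may reach the data safety and monitoring board, which reviews safety data periodically and may conduct an interim look for safety after half the patients.

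This is not a detail left open for an analysis plan. The article itself states both the sampling rule and the two measures, and following them as written produces the imbalance.

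**Working it through.** **Inputs from the protocol article.** Case rates are p = 7.4% on placebo and 3.7% on magnesium (Study objectives). There are 251 patients per arm (Sample size considerations), used here only as a denominator. Every patient has 2 post-ERCP samples (Treatment scheme). The expected number of cases is 251 × 0.074 = 18.6 and 251 × 0.037 = 9.3. The plan gives no laboratory figure to reproduce.

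**Assumptions, not in the document.** Each case has k extra samples, with the same k in both arms. The range 3 to 10 corresponds to one sample a day over the hospital stays that define mild and moderate disease (Definitions). Non-cases have no later study samples. Abnormality rates are given at each step. Magnesium has no effect on the laboratory values.

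**1. Samples per patient = 2 + p·k**

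| k | Placebo | Magnesium | Excess on placebo |
|---|---|---|---|
| 3 | 2.22 | 2.11 | 5% |
| 7 | 2.52 | 2.26 | 11% |
| 10 | 2.74 | 2.37 | 16% |

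**2. Count of out-of-range values per analyte.** Take k = 7, with 5% of values abnormal in non-cases and 50% in cases.

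- Placebo: 0.926 × 2 × 0.05 + 0.074 × 9 × 0.5 = 0.426 per patient, or about 107 per 251.
- Magnesium: 0.963 × 2 × 0.05 + 0.037 × 9 × 0.5 = 0.263 per patient, or about 66 per 251.
- The ratio is 0.62 and the gap about 41 values.

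Split by source:

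- Extra samples only: 251 × 0.074 × 7 × 0.5 = 65.0 against 251 × 0.037 × 7 × 0.5 = 32.5, a gap of 32.5.
- Scheduled samples only: 251 × (0.926 × 0.10 + 0.074 × 2 × 0.5) = 41.8 against 251 × (0.963 × 0.10 + 0.037 × 2 × 0.5) = 33.5, a ratio of 0.80.

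So 32.5/41, roughly 80% of the gap, is due to extra sampling. The remaining 8 or so values reflect the disease itself.

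**3. Shift to the most extreme value.** Let q0 be the chance that a scheduled value is abnormal, the same for everyone, and q1 the chance for an extra value, with values independent. The artefact is (0.074 − 0.037) × (1 − q0)² × (1 − (1 − q1)^k).

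- q0 = q1 = 5%, k = 5: 0.037 × 0.9025 × 0.226 = 0.76 points (11.3% against 10.5%).
- q0 = 5%, q1 = 50%, k = 5: 0.037 × 0.9025 × 0.969 = 3.23 points (16.2% against 13.0%).
- For k from 1 to 10, q0 from 5% to 20% and q1 from q0 to 100%, the range is 0.17 to 3.34 points.
- Both bracketed factors are at most 1, so the artefact cannot exceed 3.7 points.

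**4. What it could mask.** With q0 = 5%, q1 = 50% and k = 5, a magnesium effect that raises the abnormality rate at the scheduled samples by 1.78 points cancels the shift-table artefact. For the count it takes 0.037 × 5 × 0.5 / 2 = 4.6 points. Larger effects make magnesium look worse.

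**5. Common window.** If only the 6-hour and 24-hour samples are used, each arm contributes 2 × 251 = 502 values per analyte and the extra-sampling artefact is zero.

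**The case against.** Several points on the other side stand.

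- A reader might infer that the arm with fewer cases will look safer whatever magnesium does to the laboratory values. The documents do not support that. Steps 3 and 4 show a capped artefact that a large enough drug effect reverses.
- A reader might also treat the whole 107 against 66 as artefact. It is not. A ratio of 0.80 remains on the scheduled samples alone, because cases are defined partly by raised lipase and preventing pancreatitis does prevent abnormal values.
- Laboratory values are only one of two main safety measures. Adverse-event frequency is the other, and this sampling rule does not govern it.
- The laboratory summaries are descriptive, and no between-arm test is specified.
- The shift-table artefact is small against chance. At 16.2% and 13.0%, the standard error of the difference is √(0.162 × 0.838/251 + 0.130 × 0.870/251) = 3.1 points, about the size of the 3.2-point artefact.
- Taking the worst post-baseline value is a common convention meant to avoid missing late extremes.

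It can also be said that analysis windows belong in the analysis plan, which is not shown. That carries less weight here, because the article states its measures without a window alongside a sampling rule that depends on outcome. Nor does the descriptive status remove the problem: the tables will be read across arms, and this bias is systematic.

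**Conclusion.** The concern holds in a limited form. As written, both laboratory measures are biased toward the arm with fewer pancreatitis cases, even if magnesium does nothing to the laboratory values. The count of values is the more exposed measure, because one case can contribute many values.

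The direction follows from the text; the size does not. The count ratio of 0.62, and the 80% share due to extra sampling, rest on assumed k = 7 and assumed abnormality rates of 50% and 5%. The 3.7-point cap on the shift tables rests on the design case rates and on equally long continued sampling per case in both arms. It would loosen if magnesium also shortened the stay of cases. The issue is modest, but it affects a measure the plan names as a main basis for safety.

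**What to change.** In Safety considerations, or in the analysis plan with a cross-reference, state that:

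- the between-arm laboratory comparison (out-of-range results, shift tables and changes from baseline) uses the 6-hour and 24-hour samples taken in all patients;
- the out-of-range measure is the number of patients with at least one such value, not the number of values;
- the most extreme value over all samples, including those after 24 hours, is reported in a separate supplementary table by arm, with a note that later samples exist only for pancreatitis cases.

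No new data are needed. The second infusion starts 6 hours after ERCP and runs for 2 hours, so the 24-hour sample follows both infusions in every patient, although it is then essentially the only common time point after the second one. The small downside is that late extremes in pancreatitis cases appear in the supplementary table rather than the main one. The change removes the sampling artefact only; the part of the difference caused by pancreatitis itself remains, and should.
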